### Study MUR and biopsychosocial assessment protocol

During the intervention the clinical pharmacist will complete an online baseline data collection, case report form (CRF) where they will record:

➢Surgical procedure undergone (hospital, ward, date, and length of stay)➢Opioid (drug name, dose per tablet (milligram (mg)), number of tablets/patches prescribed per day (24 hrs), total number of tablets prescribed)➢Opioid use prior to surgery (drug name, dose per tablet (mg), number of tablets/patches prescribed per day (8 am to 8 am), total number of tablets prescribed), length of time on opioids➢Calculate the combined morphine equivalent dose (MME, using Faculty of Pain Medicine guidelines)
^
29
^
➢Record use of other analgesics including paracetamol, Non-Steroidal Anti-Inflammatory Drugs (NSAIDs) and other adjuvants – (drug name, dose per day)➢Determine if medically treated for depression or anxiety (if yes, drug name and dose) – taken from patient or retrieved from medical records, where applicable.➢Patient pain intensity in the last 24 hrs, measured using the Verbal Pain Rating Scale (No pain = 0; mild pain = 1; moderate pain = 2; severe pain = 3; very severe pain = 4)➢Record any coexisting morbidities and their effect on pain➢Record alcohol weekly consumption (1 – 7, 8 – 14, or >14 units*)➢Smoker (yes/no)

*One unit of alcohol is equivalent to 10 mL or 8 g of pure alcohol. E.g., 1 glass of wine (175 mL) = 2.1 units.

Following the MUR and biopsychosocial assessment, the clinical pharmacist will then decide with the patient which one of the three opioid de-escalation pathways (A, B or C) developed using various sources, American Pain Society
^
41
^, Veteran Affairs/Department of Defence
^
42
^, see also Kral
*et al.*, 2015
^
43
^ they will follow (
Figure 2). Due to a paucity of guidelines available for reference for dosage reduction or discontinuation of opioids particularly following surgery, guidance was adapted from the CDC Guideline for Prescribing Opioids for chronic pain
^
44
^; from the Veterans Health Administration Practice Guideline for Opioid Therapy in Chronic Pain
^
45
^; from the US Department of Health and Human Services Guide for Clinicians
^
46
^; and in collaboration with the local Community Chronic Pain Service.

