### Surgical opioid use

Opioids are routinely used pre-, intra-, and post-surgically for the treatment of acute pain and post-operatively for pain management and is a primary route to exposure to these types of medicines, often for the first time
^
14,
15
^. Evidence from the US and Canada has shown a clear link between post-surgical opioid prescribing for both minor and major surgery, and persistent long-term use in the community, beyond tissue healing. Inappropriate prescribing of opioids both peri- and post-operatively, accounts for 36.5% of all opioid prescribing in the US, with 3 – 10% of these patients transitioning to long-term use
^
11,
14,
16,
17
^. Patients undergoing surgery are almost four times more likely to be discharged with opioids than their non-surgical counterparts
^
18
^. This is often with more opioid medication than is actually required to treat post-surgical pain
^
19–
22
^. Perhaps more alarmingly, almost half (45%) of these patients are given opioids even though they would not have been taking any opioids at point of discharge
^
23
^. In the United States (US), a study showed that between 5.9 – 6.5% of all patients who underwent surgery (versus 0.4% of the non-surgical control) went on to become long-term opioid dependent, even if they had never taken opioids before
^
15
^.

It is becoming clear from the US, that postsurgical prescribing of opioids is a problematic, underexplored, new source of long-term opioid use
^
17
^. Compared to the US and Canada, less is known in the UK about peri-operative opioid prescribing in hospitals and any link to long-term use. Two recent studies in the UK have identified long-term opioid use (>1 year) to be associated with older age (>75 years), being socioeconomically disadvantaged, having a history of depression and/or alcoholism, prior gapapentinoid or psychotrophic use, and those initiated on >120 morphine milligram equivalents (MME) following major surgery
^
6,
24
^. There are over 5.6 million opioid prescriptions dispensed each year in the UK, corresponding to around 13% of the adult UK population
^
25
^ and over 4.7 million surgical procedures occurring each year
^
26
^ and nearly 8 million people on surgical waiting lists, with over 300,000 waiting more than 52 weeks for surgery
^
27
^. This, along with no current national guidelines on peri-operative opioid prescribing, a declining GP workforce and increasing patient numbers
^
28

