### Aims and objectives

The primary aim of this study is to evaluate a multi-centre, pharmacist-led, early opioid deprescribing intervention. This is designed for patients discharged following a surgical procedure with an opioid prescription from hospitals within a single NHS Trust in an area of high opioid prescribing, East Kent. It will determine whether this designed intervention is able to support early deprescribing of opioids in this particular healthcare setting and with this particular patient population and to inform a much larger, clinical trial. A summary of the aims and objectives for this study are collated in
Table 1.

**Table 1. T1:** Summary of study aims and objectives.

Aims/questions	Objectives
**To test the feasibility of delivering an early opioid ** **deprescribing intervention in primary care, led by ** **trained clinical pharmacists.**	**Ascertain stakeholder acceptability of the intervention:** • Maintain detailed records of any barriers or enablers that may occur in response to setting up the intervention and whilst delivering the intervention • Deliver stakeholder interviews
	**Measure the capabilities of trained clinical pharmacists to deliver an ** **early opioid medication review by**: • Completed intervention delivery training • Observational competency checks by Clinical Lead • Completed medication review case reports • Number of participants successfully deescalated
	**Ascertain participant acceptability of the intervention by measuring**: • Number of participants that enrol in the study • Number of withdrawals from the study • Adherence to pharmacist medication recommendations • Responses to participant satisfaction questionnaire • Responses during participant interviews
	**Apply a micro-costing approach to estimate the intervention costs:** • opioid medication costs • staff costs • Health resource use (primary care services, community-based services, hospital inpatient and outpatient services)
**To measure successful discontinuation and/or ** **reduction in the use of opioids to within the ** **recommended 2–4-week period for opioid use ** **or by the expected period of tissue healing (<91 ** **days) whichever is sooner ^ 39 ^.**	**Measurement of** the mean difference in morphine milligram equivalent (MME) dose at baseline and at 90 days

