**To understand post-surgical opioid prescribing ** **experiences including opioid use, long-term ** **opioid use, participant pain and quality of ** **life in the 3-month period post-surgery when ** **discharged with an opioid prescription**	• Collect medication use data at baseline and at all follow-up appointments • Compare opioid prescribing (type, dose, amount) at baseline for each surgical speciality and hospital • Measure pain scores at baseline and final visits • Measurement of risk factors in the participant population that have been previously linked to long-term opioid use ○ Baseline demographics; ○ Medical, prescription and surgical histories. • Response to Quality-Of-Life questionnaire (EQ5D-5L) complete at baseline and final appointment • Responses during participant interviews
**To ascertain the feasibility of delivering the ** **intervention as per the protocol to inform a ** **future study or adoption of the protocol**	**Measurements of:** • Time spent finding and recruiting participants • Number of possible surgical participants per week that could receive intervention • Number of pharmacists available to deliver the intervention • Number of surgical participants that accept an early MUR versus the number that are asked • Time taken from hospital discharge to receiving first MUR. • Average time taken for each appointment • Average time taken to successfully deescalate opioids in surgical patients • Number of participants that are successfully deprescribed opioids within 3 months • Number of patients that require additional appointments with the pharmacist • Number of participants that require additional support post-90 days • Responses during participant interviews

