### Statistical analysis

For the quantitative measures descriptive statistics will be used to describe the intervention population including patient demographic variables, deprivation scores, comorbidities for each surgical type, medication prescribed (including type, dose, amount, duration and long or short-acting), pain scores and history of opioid use. Descriptive statistics will also be used to assess de-escalation success rates, proportion of long-term users and quality of life. Similarly, descriptive statistics will be used to determine attrition rates at various stages and the different reasons provided. Means difference analyses will be performed via corrected repeated measures
*t*-test/Wilcoxon’s tests or mixed ANOVAs (depending on data distribution and number of participants) to test the difference of MME taken at discharge and 91-days post discharge in each of the three pathways. The allocation to pathway C or not will be treated as a dichotomous outcome variable in a set of logistic regression models to determine the significance of a number of predictors as risk factors. Chi-square analyses will be used to compare the proportion of patients who accepted or declined the intervention. For the health economic analysis, a micro-costing approach will be used to estimate the intervention costs, opioid and other analgesic medication costs, and relevant participant health resource use. The qualitative data from the interviews will be transcribed verbatim, entered into qualitative data analysis software (
NVivo v11) or Microsoft Excel 2021 and subjected to thematic analysis
^
48
^. Notes collected at each medication assessment meeting will be reviewed and analyses for themes related to recommendations for the intervention and the role of clinical pharmacists in deprescribing opioids post-surgery.

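### The stated aim concerns opioid use, but every opioid quantity listed for the MME calculation is a prescribed one, so unused supply can count as de-escalation

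*Protocol article*

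**What the plan says.** Table 1 (Aims and objectives) sets out to measure discontinuation of opioids or reduction in their use, through the "mean difference in morphine milligram equivalent (MME) dose at baseline and at 90 days". Outcome 5 in Table 3 (Outcomes measures) is the percentage of participants who reduce or stop opioids within 91 days. The Statistical analysis section plans tests of the "difference of MME taken at discharge and 91-days post discharge in each of the three pathways".

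The inputs are listed under Study MUR and biopsychosocial assessment protocol. For the current opioid the pharmacist records drug name, strength per tablet and the "number of tablets/patches prescribed per day (24 hrs), total number of tablets prescribed". Use before surgery is also recorded as a prescribed quantity: "Opioid use prior to surgery (drug name, dose per tablet (mg), number of tablets/patches prescribed per day (8 am to 8 am". On the same form the pharmacist is to "Calculate the combined morphine equivalent dose (MME, using Faculty of Pain Medicine guidelines". Other analgesics, by contrast, are recorded as use, with a dose per day.

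For follow-up, the Data collection section names pain scores, changes to medication and symptom management. Table 1 separately commits to "Collect medication use data at baseline and at all follow-up appointments", without saying what the item is.

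**The concern.** Prescribed dose and intake can differ widely in this population, and the protocol says so itself. The Surgical opioid use section states that patients often leave hospital with more opioid than they need, and that "almost half (45%) of these patients are given opioids even though they would not have been taking any opioids at point of discharge". Pathway C expects post-surgical pain normally to settle within 3–4 days, whereas Study design and setting puts the first review 7–10 days after discharge. Eligibility depends on being discharged with an opioid, not on still taking it. People who have already stopped can therefore enrol.

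With prescribed MME as baseline, such a person starts at the full dose and ends at zero without any change in use. Someone still taking leftover hospital tablets after the prescription has ended could be recorded as stopped. Both errors favour the intervention, and there is no control arm in which they would also appear. The MME change and the de-escalation rate are meant to inform a much larger trial, so an inflated value would carry over into its design.

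**Working it through.** The protocol gives no MME mean, standard deviation or expected change, so there is no stated figure to reproduce. The check is an identity followed by an illustration.

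**Identity.** Let P be the prescribed MME, T the MME taken and X91 whatever is recorded at day 91.

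- Recorded change = P0 − X91. True change in use = T0 − T91.
- If day 91 records intake (X91 = T91), the excess is P0 − T0.
- If day 91 records the prescribed dose (X91 = P91), the excess is (P0 − T0) − (P91 − T91). It cancels when the unused amount is the same at both times.
- For anyone who has truly stopped and has no prescription (P91 = T91 = 0), the excess is again P0 − T0.
- For anyone still taking leftovers with no prescription (P91 = 0, T91 > 0), it is P0 − T0 + T91.

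The excess is upward whenever baseline intake is below the prescribed dose, unless an equal or larger unused amount is still prescribed at day 91.

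**Illustration.** Let u be the share taking none at baseline and f the fraction of the prescribed dose taken by the rest. Then T0 = P0 × (1 − u) × f, the overstatement is P0/T0 = 1/((1 − u)f), and the spurious share of a fall to zero is 1 − (1 − u)f. Take an assumed prescribed baseline of 30 MME/day, everyone at zero on day 91, and f = 1:

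| u | MME taken | Overstatement | Spurious share |
|---|---|---|---|
| 0 | 30 | 1.00 | 0% |
| 0.10 | 27 | 1.11 | 10% |
| 0.25 | 22.5 | 1.33 | 25% |
| 0.45 | 16.5 | 1.82 | 45% |

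The ratios do not depend on the assumed 30. If takers use less than the full dose, the excess grows: u = 0.45 with f = 0.5 gives T0 = 8.25, an overstatement of 3.64 and a spurious share of 72.5%. Only u = 0.45 has a source in the document, and that is a background figure. The other values are assumptions.

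**Outcome 5.** If non-users are all counted as reduced or stopped, they contribute u × N successes. With u from 0.10 to 0.45 that is 8 to 36 of 80, or 10 to 45 of 100. If s is the success rate among actual users, the recorded rate is u + (1 − u)s, which exceeds s by u(1 − s). The inflation is at most u, and it shrinks as more of the actual users succeed.

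**The case against.** The strongest reply is that the article condenses a fuller protocol and shows neither the baseline CRF nor the follow-up form. Table 1 promises medication use data at every visit and lists adherence to the pharmacist's recommendations. The pathway criteria turn partly on how long the patient has been taking opioids, so the pharmacist must ask about use. The follow-up list is not worded as exhaustive. This stands: a reader might infer that intake is never recorded and that the bias cannot be repaired, but the document does not show that.

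Second, the phrase "to test the difference of MME taken at discharge and 91-days post discharge" can be read as a measurement taken at those times, and Table 1 says only dose. Prescribed dose at both times would be a coherent measure for a deprescribing study. This stands in part. It makes the wording ambiguous, but the aim and outcome 5 are still about use, and the listed inputs do not measure it.

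Third, 45% is a cited background figure describing status at discharge. It does not say that those patients took nothing later at home, and people who agree to an opioid review may differ. This stands: 45% cannot be used as this cohort's rate.

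Fourth, the primary outcome is feasibility, reduce-or-stop is one of seven outcomes and is not said to be computed from CRF MME, and an uncontrolled fall could not establish an effect on either basis. This lowers the severity but does not remove the problem, because the figures are still intended to inform the next trial.

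**Conclusion.** The point holds conditionally. The article is more than silent here: it itemises the opioid fields and fixes each quantity as prescribed, while the aim and outcome 5 concern use. If MME and outcome 5 are derived from those fields, unused supply is counted as de-escalation, and the error runs in the favourable direction.

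The size is unknown. The range of 1.11- to 1.82-fold, with 10–45% of a fall to zero being unused supply, rests on assumed non-use of 10–45%, full-dose intake by everyone else and everyone at zero on day 91. It is not an estimate for this study. The document does not support saying that nearly half of the recorded reduction will be artefact, or that intake data certainly do not exist. This should be fixed before more participants are enrolled, but it does not undermine the feasibility objectives.

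**What to change.** 1. **Record intake.** At baseline and every follow-up, enter actual opioid intake beside the prescribed dose: tablets or liquid taken in the last 24 hours and the number remaining; for patches, whether one is worn and its strength. If the full CRF already does this, say so and name the item.
2. **Use one basis.** Define outcome MME as intake at the first review and at day 91. This moves the baseline away from discharge, so reconcile it explicitly with the Statistical analysis section and with the baseline-to-90-days wording in Table 1. Keep discharge MME as a description of prescribing.
3. **Fix the denominator.** Report participants with zero intake at the first review on their own line. Give the reduce-or-stop percentage among those using opioids at the first review, alongside the figure for all enrolled.
4. **Participants already enrolled.** The Study status section reports 18 recruited by 23 July 2024. For any without intake data, label MME as prescribed and analyse them separately.

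The cost is two or three CRF fields and a minor amendment. The headline reduction will probably be smaller, and fewer participants will have an intake-based MME.

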**Figure 2. f2:**
[figure not shown]
Intervention pathways and guidelines flow chart. N.B. These are just guidelines and subject to adjustment by the participating practices and pharmacists. *The pharmacist may also prescribe/recommend other pharmacological approaches to deal with: aches/pains – NSAIDs: Ibuprofen, 400mg/3X/daily or paracetamol, 1000 mg, every 6 hours; diarrhoea – Loperamide 2-4 mg as needed (up to 16 mg/day); constipation – laxative, as and when needed. Abbreviations: MME – morphine milligram equivalent; SAE – serious adverse event; hr – hour; mcg – microgram; NSAIDs – non-steroidal anti-inflammatory drugs. Image created by Biorender.com.

### Pathway A – Rapid opioid de-escalation

For this pathway the clinical pharmacist may recommend immediate discontinuation of opioids if any of the following apply:

➢Patient has been taking opioids for less than 7 days post-discharge and combined MME is less than < 30 mg/day (see
Table 1).➢Opioids were not being used prior to surgery.➢Patient has no history of alcohol or substance abuse.➢The acute pain condition following surgery has resolved.➢The patient requests discontinuation of opioids.➢The patient has developed intolerable side effects from taking opioids.➢
*****The patient is at risk of a serious adverse event (SAE), such as overdose (refer to specialist service).➢
*****There is evidence of opioid diversion (refer to specialist service).

*****Specialist services are required to manage these complex patients and will be referred to the Clinical Lead for guidance and recommendation.

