### Pathway B – Gradual de-escalation of opioids

For this pathway the clinical pharmacist may recommend ‘gradual’ discontinuation of opioids if any of the following apply:

➢Patient has been taking opioids for more than 7 days and/or the combined MME is more than > 30 mg – 120 mg/day or ≥12 µg/hr transdermal Fentanyl patches or ≥15 microgram (mcg)/hr Buprenorphine patches➢The medication is not providing useful pain relief and function has not improved➢Patient was taking opioids prior to surgery to treat pain related to their condition.➢Presents with other co-morbidities including mental health disorders➢Patient has a history of alcohol or substance abuse➢Patient is taking other medications (e.g., benzodiazepines, gabapentin, pregabalin or muscle relaxants) or medical conditions (lung disease, sleep apnoea, liver disease, kidney disease, fall risk, advanced age) that could increase the risk of adverse events (AEs)➢Patient requests a dosage reduction of their opioids➢The pharmacist feels it is safer to start with a gradual de-escalation of opioids

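### Under Pathway A's *any* rule, no abuse history alone or no prior opioid use alone nominally supports immediate stopping at any eligible dose, bypassing A's own 30 mg/day limit

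*Protocol article*

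**What the plan says.** All places are in the Protocol article.

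- **Pathway A – Rapid opioid de-escalation.** The rule is "the clinical pharmacist may recommend immediate discontinuation of opioids if any of the following apply". The first item is "Patient has been taking opioids for less than 7 days post-discharge and combined MME is less than < 30 mg/day". The second is "Opioids were not being used prior to surgery" and the third is "Patient has no history of alcohol or substance abuse". The others are resolved acute pain, patient request, intolerable side effects, risk of a serious adverse event, and diversion. The last two carry referral to a specialist service.
- **Pathway B – Gradual de-escalation of opioids.** This list is also met by any one item. Its dose and duration item begins "Patient has been taking opioids for more than 7 days and/or the combined MME is more than > 30 mg – 120 mg/day". Two further items are "Patient was taking opioids prior to surgery to treat pain related to their condition" and "Patient has a history of alcohol or substance abuse". It also has a discretion item: "The pharmacist feels it is safer to start with a gradual de-escalation of opioids".
- **Pathway C – Continuation of opioids.** The closing paragraph says that the pathways are not exclusive and that patients may move between A and B. It expects most first-time users with post-surgical pain to need no complex protocol. It adds that people with earlier use (up to 90 days) or a higher dose may need a slower withdrawal or specialist referral.
- **Eligibility criteria.** Patients may enter on up to 120 mg MME/day. More than 90 days of opioid use before surgery is an exclusion, so shorter prior use is allowed.

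**The concern.** The second and third Pathway A items state that a risk is absent. They read naturally as safeguards on the low-dose, short-duration item. Having no abuse history is not in itself a reason to stop an opioid at once, whereas resolved pain, a patient's request or intolerable side effects are. Under *any*, each of the two becomes sufficient alone, and the 30 mg/day limit no longer binds anyone who meets either.

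The two items also mirror two Pathway B risk items, prior use and abuse history. A prior user without an abuse history therefore qualifies for A on one item and for B on the mirror of the other.

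The main stake is patient safety: the text gives nominal support for abrupt cessation at doses that the protocol elsewhere steers towards tapering. There are also two consequences for the evaluation. Table 3 includes fidelity of the intervention and transferability of the protocol as outcomes. Where A and B are both met, either choice conforms, so fidelity of pathway selection is hard to judge. The Statistical analysis section also tests change in MME in each pathway, and loose entry rules blur those groups.

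**Working it through.** The plan gives no figure to reproduce. The check reads the printed lists as logical conditions and applies them to illustrative patients.

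**Inputs**

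- A1: less than 7 days since discharge *and* below 30 mg MME/day. A2: no opioid use before surgery. A3: no abuse history. (Pathway A)
- A is met if A1 or A2 or A3 or any of the remaining five items holds. (Pathway A)
- B1: more than 7 days of use and/or above 30 and up to 120 mg/day. Separate B items cover prior use for the same condition and abuse history. (Pathway B)
- Eligible dose: up to 120 mg/day. (Eligibility criteria)

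Each patient below takes 60 mg MME/day and is seen on day 8. None of the other five Pathway A items applies.

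| Patient | A1 | A2 | A3 | A as printed | B items met |
|---|---|---|---|---|---|
| No prior opioids, no abuse history | no | yes | yes | met | dose/duration |
| Prior use for the surgical condition, no abuse history | no | no | yes | met | dose/duration, prior use |
| No prior opioids, abuse history | no | yes | no | met | dose/duration, abuse history |

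A1 fails in every row because 60 is not below 30. Neither A2 nor A3 refers to dose, so the result is the same at any dose above 30 and up to 120 mg/day. The second row shows the wider reach of A3: it takes in a prior user, whom both Pathway B and the closing paragraph of Pathway C steer towards gradual reduction.

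**With the three items joined**

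Replace A1 or A2 or A3 by (A1 and A2 and A3), and keep the other five items as separate triggers. A1 is false in all three rows, so none meets A on these items, and all three still meet B. Making all eight items joint would not work, because patient request, side effects, adverse-event risk and diversion are each meant to act alone.

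**A side effect to check**

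Take a patient below 30 mg/day with no prior opioids and no abuse history, seen on day 8, having used opioids since discharge. As printed, A is met through A2 and A3. After joining, A1 fails because 8 is not less than 7, and this low-risk patient would lose A unless another trigger applied. The Abstract and the study design paragraph place the first review within 7–10 days of discharge, and Study interventions places it within ten days. The day limit therefore has to be considered together with the join.

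**The case against.** The strongest reply has four parts.

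1. **Rationale for first-time users.** The Pathway C section expects most such patients to need no complex de-escalation. That gives some reason for the no-prior-use item. It does not cover the abuse-history item, and the same paragraph separately names higher doses as possibly needing a slower course.
2. **Overlap is intended.** The pathways are expressly non-exclusive, and a patient can move from A to B. Qualifying for both is therefore not a fault in itself. A later move does not undo an initial abrupt stop, however, and non-exclusivity does not put a dose condition on the two items.
3. **Discretion and safeguards.** Both lists say *may*. The pharmacist decides with the patient. The Figure 2 legend calls the pathways guidelines open to local adjustment, and B has its own safety item. Pharmacists are recruited with deprescribing experience, long prior use and methadone or injecting history are excluded, and untoward events that could be related to the intervention are reported within 24 hours. All of this stands and limits the likely harm.
4. **Figure 2.** It is not shown and may put the criteria in order. The point therefore rests on the text alone, and a reader should not infer that no precedence rule exists. If the figure has one, the text should agree with it.

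A reader might also infer that the low-dose item can never be met at the planned review. The documents do not support that. A review within 7–10 days can be read as an outer limit, Study interventions says within ten days, and Recruitment looks for patients discharged in the last 7 days, so a visit before day 7 is possible.

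**Conclusion.** The point holds for the printed wording. Either absence-of-risk item alone nominally supports immediate stopping up to the 120 mg/day entry ceiling. This bypasses A's own limit of 30 mg/day and overlaps B's dose range. The abuse-history item is the weaker of the two, because it also admits prior users and the protocol offers no rationale for it as a stand-alone trigger.

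The size is modest: a minor safety correction of wording. The documents give no dose distribution and no frequencies of prior use or abuse history, so the number of participants affected is unknown. The illustrative patients show what the wording allows. They say nothing about how often it happens.

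A reader might go further and infer that the protocol directs abrupt cessation at high doses or flatly contradicts itself. It does neither: both pathways are permissive, and the expectation of slower withdrawal is also stated as a possibility. Nor do the documents support a mandatory taper above 30 mg/day, which would be a clinical preference.

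The conclusion assumes that *any* is read literally and that Figure 2 does not already impose the joint condition.

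**What to change.** In Pathway A, make no prior opioid use and no abuse history conditions joined to the low-dose, short-duration item under *all of*. Keep resolved pain, patient request, intolerable side effects, risk of a serious adverse event and diversion as separate triggers, with the existing referral for the last two.

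When joining the items, check that the 7-day limit suits the review timing, so that low-dose patients without prior opioid use who are seen on days 7–10 are not shut out of A. The clinical team should set the value. Align Figure 2 if it repeats the present wording.

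The cost is a short wording amendment, possibly with ethics review. The study was already recruiting (18 participants by 23 July 2024), so those enrolled before the change were assigned under the present wording. The pathway-specific MME results should say which wording applied to whom.
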